## Abstract

**Objective::**

The objective of this current research is to investigate the effectiveness of the nursing intervention of combination gelatin sponge and moist wound healing in treating the pressure ulcers (PUs).

**Methods::**

This is a randomized controlled trial to be carried out from January 2021 to May 2021. This trial is implemented in accordance with the SPIRIT Checklist for the randomized researches and was granted through the Ethics Committee of 5th Medical Center of Chinese PLA General Hospital (No. 0624876). This study includes 80 PU participants. The patients meet the following criteria will be included. All participants meet the diagnostic criteria recommended via the National Pressure Ulcer Advisory Panel Society: complete skin defect, no bones, tendons and muscles exposure, no subcutaneous tunnel or scale; the patients selected are between 40 and 60 years old. The patients with the following criteria will be excluded: receiving other treatments that may influence the healing, for instance, radiation therapy and corticosteroids; patients with the complications of infection, malignant tumors, as well as peripheral vascular disease; and patients with serious diseases, containing kidney, cardiac, and liver diseases. The patients are randomly divided into 2 groups, the control group and study group, with 40 members in each group. In control group, the patients are given the routine nursing care. And in study group, the patients are given the nursing of gelatin sponge combined with moist wound-healing. After 28 days, the state of the patients healing is observed closely, containing the dressing change frequency, curative effects, and the end-point efficiency. On the basis of the Pressure Ulcer Healing Scale developed by the American pressure sore expert group, the quantitative scoring can be implemented, and therapeutic effects are assessed.

**Results::**

The variables of clinical result among the groups are illustrated in the Table.

**Conclusion::**

The nursing intervention of gelatin sponge combined with the moist wound- healing may evidently increase the healing efficiency of PU.

**Trial registration number::**

researchregistry 6091.

## Introduction

1

The pressure ulcers (PUs) are the skin necrosis areas, which can influence the deep tissues (for instance, the subcutaneous muscles) and/or the superficial tissues (the epidermis and dermis).^[1,2]^ These lesions occur in the interruption of local blood supply, resulting in the local oxygen and nutrition deficiency.^[3,4]^ This vascular rupture is usually caused by the moderate acute or chronic local high pressure in skin. Recently, the epidemiological data on the PUs in US are relatively limited, whereas the incidence rate is estimated to be between 1 million and 3 million annually.^[5]^ Among all the hospitalized patients, the difference of reported prevalence is obvious, which affects 5% to 15% of the patients in total, but the proportion of patients affecting intensive care units remains high.^[6]^

PUs have been receiving more and more attention. They are an important source of mortality, and they continue to bring a great burden to health care systems and patients. Although PUs are usually the result of general poor health and other diseases, it can be avoided in many cases.^[7]^ Therefore, prevention of PU is our goal, which is all more important in view of the high treatment cost and challenges. The basic elements of the effective prevention methods contain the frequent repositioning, the application of proper supporting surfaces, appropriate nutrition as well as the management of moisture.^[8]^ Gelatin sponges is a kind of absorbable medical dressings, which is utilized for the hemostasis of bleeding surfaces.^[9]^ Such dressing is a kind of water-insoluble, off-white, flexible, and inelastic material, which is derived from cowhide or pig skin. Gelatin sponge can absorb a lot of blood as well as some other fluids. It can promote the tissue healing rapidly and is extensively utilized in the engineering of tissue.^[10,11]^ There are few researches on the application of gelatin sponge in PU. The objective of this current research is to investigate the effectiveness of the nursing intervention of combination gelatin sponge and moist wound healing in treating the PUs.

## Materials and methods

2

### Study design

2.1

This is a randomized controlled trial to be carried out from January 2021 to May 2021. This trial is implemented in accordance with the SPIRIT Checklist for the randomized researches and was granted through the Ethics Committee of 5th Medical Center of Chinese PLA General Hospital (No. 0624876), and this trial was registered with research registry (researchregistry6091).

### Patients and randomization

2.2

This study includes 80 PU patients. A random number is assigned to all the patients through utilizing via using a random number table, and the allocation result is hidden in a random envelope. The patients are randomly divided into 2 groups, the control group and study group, with 40 members in each group. The patients meet the following criteria will be included. All participants meet the diagnostic criteria recommended via the National Pressure Ulcer Advisory Panel Society: complete skin defect, no bones, tendons and muscles exposure, no subcutaneous tunnel or scale; the patients selected are between 40 and 60 years old. The patients with the following criteria will be excluded: receiving other treatments that may influence the healing, for instance, radiation therapy and corticosteroids; patients with the complications of infection, malignant tumors, as well as peripheral vascular disease; and patients with serious diseases, containing kidney, cardiac, and liver diseases.

### Nursing methods

2.3

In control group, the patients receive the routine nursing care. Iodine or hydrogen peroxide is utilized for the mechanical debridement and local disinfection to remove purulent secretion in the necrotic tissues. The latent cavity of lacunar pressure sore is filled with ethacridine gauze. The wound is covered via using the aseptic dressing, and such dressing should be changed every 1 to 2 days.

In study group, patients are given the nursing of the combination of gelatin sponge and moist wound-healing. The wound surface is cleaned by using cotton ball and normal saline. The yellow surface of the wound is cleaned through the surgical debridement in order to carry out the excision of necrotic tissues and the gelatin sponge can absorb the exudate, and then it covers the wound. If infected, the yellow surface could be covered with gelatin sponge soaked in the silver ion sodium alginate and then carefully examine the skin inside or around the dressing. If the leakage is occupied, the milky white area is more than one-third, and the sponge should be replaced in time (once/1--2 days) after the emergence of novel granulation tissue on sponge. Clean the area again once a week to apply gelatin sponge. Gently to strengthen the humanized care, the patients are turn over slowly every 2 hours, raising the bedside to keep the angle within 30° to prevent the excessive force on sacrococcygeal region. The patients are maintained smooth and dry, and the air cushion bed can improve the patient's overall nutritional status. Afterwards, the patients are given the health education before discharge. In addition, patients and their related family members are also informed of some PU risk factors.

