## Discussion

4

PU risk areas are usually regarded to appear in anatomical positions with almost no soft tissue coverage on the bone protrusions.^[13,14]^ In these areas, smallest tissue coverage does not allow the appropriate absorption and the pressure redistribution, thus they are sensitive to the pressure sores and ischemia. Patella, greater trochanter, calcaneus, ischial tubercle, and lateral malleolus are the high-risk anatomical areas for PU in the patients.^[15]^

Conventional cleaning, disinfection as well as some other generally utilized medical gauze, cannot be degraded in the vivo, and prescription includes light powder, which is toxic to kidney and liver.^[16]^ Tissue fluid can be effectively absorb by the gelatin sponge. The gelatin sponge can promote the platelet rupture, and release a large number of the coagulation factors, thereby promoting the coagulation of blood. Furthermore, the gelatin sponge can support the blood block for the prevention of the blood block from decreasing, leading to anastasis. And it is also a kind of excellent drug carrier. Published studies have indicated that it can promote the healing of wound in comparison with gauze or the traditional Chinese medicine.^[17]^ Our study program can offer a strong basis for nursing intervention of gelatin sponge combined with the moist wound-healing in treating the PU.

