## Conclusion

5

The nursing intervention of gelatin sponge combined with the moist wound healing may evidently increase the healing efficiency of PU.

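### Extra pressure-relief care is written into the study arm only, so the trial can test the whole nursing package but not gelatin sponge plus moist wound healing, which its objective names

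*Protocol article*

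**What the plan says.** Section 2.3 (Nursing methods) has one paragraph per arm.

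- **Control.** "In control group, the patients receive the routine nursing care". What follows is local wound treatment only: iodine or hydrogen peroxide debridement and disinfection, ethacridine gauze in cavities, and an aseptic dressing changed every 1 to 2 days.
- **Study group.** The paragraph sets out saline cleansing, surgical debridement and gelatin sponge, and then moves to general care: "Gently to strengthen the humanized care, the patients are turn over slowly every 2 hours". The bed angle is held within 30° "to prevent the excessive force on sacrococcygeal region". Keeping the patient dry, an air cushion bed, health education before discharge and risk-factor information for families come after that.

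The stated aim, in the Introduction, is to "investigate the effectiveness of the nursing intervention of combination gelatin sponge and moist wound healing in treating the PUs". The Abstract uses nearly the same words. Section 5 concludes: "The nursing intervention of gelatin sponge combined with the moist wound healing may evidently increase the healing efficiency of PU".

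**The concern.** Turning, bed angle and support surface act on pressure, not on the wound bed. They are not part of a gelatin sponge dressing or of moist wound healing on any ordinary reading. The document itself gives pressure a central role. The Introduction says of the vascular injury: "This vascular rupture is usually caused by the moderate acute or chronic local high pressure in skin". The Discussion says of high-risk sites that thin tissue cover "does not allow the appropriate absorption and the pressure redistribution, thus they are sensitive to the pressure sores and ischemia". Section 2.2 also excludes patients on other treatments that could affect healing, so the authors accept that co-treatment can distort the comparison.

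If controls receive less offloading, the contrast between arms is the sum of a wound-treatment effect and an offloading effect. Both are fixed by allocation, so no analysis of a two-arm trial can separate them. Post-treatment ulcer area and wound complications, both listed in Table 1, are outcomes that offloading could plausibly change. A positive result would be reported as evidence for the sponge and moist healing even if neither did anything.

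**Working it through.** **Step 1. Components by arm, from section 2.3**

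| Component | Study group | Control group |
|---|---|---|
| Cleansing | Saline | Iodine or hydrogen peroxide |
| Debridement | Surgical | Mechanical |
| Dressing | Gelatin sponge (with silver alginate if infected) | Ethacridine gauze in cavities, aseptic dressing |
| Turning | Every 2 hours | Not stated |
| Bed angle | Within 30° | Not stated |
| Air cushion bed | Yes | Not stated |
| Skin kept dry | Yes | Not stated |
| Health education, family information | Yes | Not stated |

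The first three rows can be taken as the wound strategy under test and are not criticised here. The last five are background care, written for one arm only.

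**Step 2. What the contrast estimates**

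Let W be the effect of the wound strategy, B the net between-arm effect of background care, and W×B any interaction. The trial estimates W + B + W×B. The objective and conclusion speak of W. The two agree only if background care is the same in both arms or has no effect, and the document establishes neither.

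**Step 3. Illustration of size**

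The document gives no effect size, SD or power, so there is no stated figure to reproduce.

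Inputs: n = 40 per arm (section 2.2) and significance at P<.05 (section 2.5). Assumptions: a two-sided t test on a continuous outcome, W = 0, and a net background-care effect of d SD.

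- Standard error of the difference in SD units: √(2/40) = 0.2236.
- Smallest observed difference reaching P<.05: t(0.975, 78 df) × 0.2236 = 1.991 × 0.2236 = 0.445 SD.
- Noncentrality: d / 0.2236. The power of the t test on 78 df follows.

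| Net d (assumed) | Noncentrality | Probability of P<.05 |
|---|---|---|
| 0 | 0 | 0.050 |
| 0.10 | 0.447 | 0.073 |
| 0.15 | 0.671 | 0.102 |
| 0.20 | 0.894 | 0.143 |
| 0.25 | 1.118 | 0.197 |
| 0.30 | 1.342 | 0.263 |
| 0.50 | 2.236 | 0.598 |

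A normal approximation gives nearly the same values: 0.145, 0.269 and 0.609 at d = 0.2, 0.3 and 0.5. The rows at 0.10, 0.15 and 0.25 also show what remains of 0.2, 0.3 and 0.5 if routine care already supplies half of the benefit.

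These probabilities are power to detect a real package effect, not an inflated type I error. A larger trial makes the misattribution more likely. At d = 0.30 with 80 per arm, the noncentrality is 0.3/√(2/80) = 1.90 and the probability rises from 0.26 to about 0.47.

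**The case against.** **The difference is read partly from silence.** Routine nursing care may already include turning and a proper support surface; the Introduction lists such measures among the basics of prevention. A journal article need not itemise routine care, and the study-arm sentences say only that patients are turned. Part of this stands: the true gap in offloading is unknown and could be small. But these measures are not simply left out. They are prescribed, in one arm's paragraph, and introduced as strengthening care. No equal standard is set for controls.

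**The objective can be read as the package.** The article speaks throughout of a nursing intervention, and section 2.3 could be taken to define it. That reading is possible, and the package comparison is valid. It also means the objective and conclusion need to say so, because as worded they name two components only.

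**The line between components is arbitrary.** Debridement and antiseptics also differ between arms and are not named in the objective either. It is true that equalising background care would support attribution to the wound strategy as a whole, not to the sponge alone. Still, cleansing, debridement and dressing reasonably belong together as wound management, while turning, bed angle and bed type do not.

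**The harm is not shown from the document.** The cited text concerns how ulcers arise, not how fast existing ones heal, and every d above is assumed. Both points are correct. The figures show a range and do not carry the argument, which rests on what the two arms are prescribed.

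**Conclusion.** The concern holds. Followed as written, the plan compares a multicomponent nursing package with routine care, and that comparison is valid. It cannot support the narrower statement that gelatin sponge plus moist wound healing produced the benefit, because any between-arm difference in offloading is inseparable from it.

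The size cannot be fixed from the document. Under the assumptions above, the chance of a significant result that owes nothing to the wound strategy runs from 5% (equal background care) to about 60% (net 0.5 SD), with 14% at 0.2 SD and 26% at 0.3 SD.

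This must be fixed, because it concerns the trial's central causal claim and attribution cannot be recovered once care has been given. Confidence is medium, since the offloading that controls actually receive under routine care is not stated.

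**What to change.** **Preferred.** In section 2.3, take background care out of the study-group paragraph and state it once, for example:

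*Both groups receive the same background care: repositioning every 2 hours, bed angle within 30°, air cushion bed, skin kept clean and dry, and health education before discharge, with risk-factor information for families.*

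The arms then differ only in cleansing, debridement and dressing.

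The cost is one change of wording plus this care for controls who do not already get it: at most 24/2 = 12 turns a day, or 12 × 28 = 336 per patient over 28 days; air cushion beds for up to 40 controls; and the education sessions. The observed contrast may shrink.

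**Alternative.** If equal background care is not feasible, restate the objective (Abstract and Introduction), the corresponding sentence of the Discussion and the conclusion (Abstract and section 5) as a comparison of a multicomponent nursing package, listing its parts, with routine care. This costs wording only but gives up attribution to the wound strategy.

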### Observation indices

2.4

After 28 days, the state of the patients healing is observed closely, containing the dressing change frequency, curative effects, and the end-point efficiency. On the basis of the Pressure Ulcer Healing Scale ^[12]^ developed by the American pressure sore expert group, the quantitative scoring can be implemented, and therapeutic effects are assessed.

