### Statistical analysis

2.5

All the analyses are implemented with SPSS for Windows Version 19.0. And the data are represented by using proper features, for example, percentage, standard deviation as well as mean. Mann--Whitney *U* test and independent samples *t* test are utilized for comparison between the study and control groups. In order to compare the categorical variables between study and control group, we utilize the Chi-square test. For the significance level, the value of *P* needed to be less than .05.

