## Results

3

The variables of clinical result among the groups are illustrated in the Table 1.

**Table 1 T1:** The clinical outcome variables between groups.

Variables	Study group (n = 40)	Control group (n = 40)	*P*
Branden scores			
Pretreatment			
Post-treatment			
Area of pressure sore			
Pretreatment			
post-treatment			
Frequency of dressing			
Average costs			
Wound complications			

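### No pretreatment Pressure Ulcer Healing Scale score is named and no adjustment is planned, so the day-28 comparison is valid but less precise than it could cheaply be

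*Protocol article*

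**What the plan says.** Four places in the protocol article bear on this.

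- **Section 2.4, Observation indices** (repeated in the abstract) gives a single time: "After 28 days, the state of the patients healing is observed closely, containing the dressing change frequency, curative effects, and the end-point efficiency". The next sentence names the Pressure Ulcer Healing Scale as the basis on which "the quantitative scoring can be implemented, and therapeutic effects are assessed". That sentence carries no time point of its own and mentions no score before treatment.
- **Section 3, Table 1**, titled "The clinical outcome variables between groups", has pretreatment and post-treatment rows for two measures, "Branden scores" and "Area of pressure sore". It has no row for the Healing Scale at either time.
- **Section 2.5, Statistical analysis** lists the Mann-Whitney test, the independent-samples t test ("test are utilized for comparison between the study and control groups") and the chi-square test for categorical variables. No covariate and no change from baseline is mentioned. The P value "needed to be less than .05" for significance.
- **Section 2.2, Patients and randomization** allocates 80 patients by random number table, "with 40 members in each group". It describes no stratification by wound size or severity.

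**The concern.** The scale is the article's stated means of judging whether treatment worked, yet a starting value on it appears nowhere. The authors do name baselines for two other measures, so this is not simply an article that leaves out every pretreatment reading.

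A single end-of-treatment score mixes two things: how severe the wound was at entry and what happened to it afterwards. Between randomized arms this does not bias the comparison, but it leaves the variation in starting severity in the error term. With 40 per arm and no stratification described, a chance difference in starting severity can also carry through to the day-28 result. Without a first score, no patient's change on the scale can be reported.

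The timing matters because a score of the untreated wound can be taken only before the section 2.3 care begins with cleaning and debridement. A later analysis plan can choose how to use a baseline score but cannot create one.

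**Working it through.** The article gives no power, effect size or SD, so there is no figure of its own to reproduce.

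**Reading the text.** Across the abstract and sections 2.2 to 3:

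- times stated for observing healing: 1 (after 28 days);
- mentions of a pretreatment Healing Scale score: 0;
- Healing Scale rows in Table 1: 0;
- Table 1 measures with both pretreatment and post-treatment rows: 2;
- analyses that adjust for a baseline value: 0.

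**Inputs for the size of the loss.**

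- n = 40 per arm (section 2.2).
- Significance level 0.05 (section 2.5). The sidedness is not stated; two-sided is assumed.
- Power 80%: assumed.
- Correlation r between baseline and day-28 scale score: not given; assumed 0.5 to 0.7.

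**Detectable difference, day-28 score only.** For a two-sample t test, the normal approximation is (1.96 + 0.84) × sqrt(2/40) = 2.80 × 0.224 = 0.63 SD. The exact t calculation gives 0.634 SD.

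**Detectable difference with the enrolment score as covariate.** The residual SD shrinks by sqrt(1 − r²), and the equivalent unadjusted sample size is 40/(1 − r²).

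| r | sqrt(1 − r²) | Detectable difference | Equivalent n per arm |
|---|---|---|---|
| 0.5 | 0.866 | 0.634 × 0.866 = 0.549 SD | 40/0.75 = 53 |
| 0.6 | 0.800 | 0.634 × 0.800 = 0.507 SD | 40/0.64 = 63 |
| 0.7 | 0.714 | 0.634 × 0.714 = 0.453 SD | 40/0.51 = 78 |

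**Chance imbalance.** The baseline difference between arms has SD sqrt(2/40) = 0.224, in units of the baseline SD. The probability of an absolute difference of at least 0.3 SD is P(|Z| ≥ 0.3/0.224) = P(|Z| ≥ 1.34) = 0.18. In an unadjusted comparison, an imbalance of 0.3 SD moves the day-28 difference by r × 0.3, which is 0.15 SD at r = 0.5 and 0.21 SD at r = 0.7.

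**Why these gains are upper bounds.** The table compares full adjustment with none. Pretreatment sore area is already planned. If area has correlation a with the day-28 score, adjusting for area alone already brings the detectable difference down to 0.634 × sqrt(1 − a²), and the scale baseline adds only what area does not explain. The article gives no value for a. It also plans no adjustment for area, so the 0.634 SD row describes the analysis as stated.

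**The case against.** The strongest objection is that the missing baseline is inferred from silence. A reader might conclude that the scale is scored only after 28 days. The text does not say so:

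- The scoring sentence has no time point.
- Section 2.4 is plainly not a full schedule. It also omits the pretreatment "Branden scores" and area readings that Table 1 shows are planned, and its day-28 sentence includes dressing change frequency, which can only accumulate during treatment.
- Table 1 omits the scale at both times, so the absence of a pretreatment row tells us nothing specific about baseline.
- A condensed article may leave visit timing to the full protocol.

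All of this stands, and it rules out claiming that no baseline score will be taken.

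A reader might go further and infer that healing cannot be derived for any patient, or that no later analysis could help. The documents do not support that either. No section defines therapeutic effect, curative effect or end-point efficiency as a change in the score. Change in sore area can be derived from Table 1. Randomization keeps a day-28 comparison unbiased without a baseline. Pretreatment area can serve as a partial covariate, and Table 1 would reveal an imbalance in it. Eligibility, which requires a complete skin defect without exposed bone, tendon or muscle, also narrows the range of starting severity.

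What the objection leaves untouched is the stated analysis. If a baseline score is taken, section 2.5 as written does not use it; if it is not taken, it cannot be used. The loss of precision follows either way.

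**Conclusion.** The point holds as one of precision and of protection against chance imbalance, not of validity. The measure named for judging therapeutic effect has no stated baseline and is to be compared by unadjusted tests. Under the assumptions above (80% power, two-sided 5%, r of 0.5 to 0.7), the detectable difference with 40 per arm is about 0.63 SD, against 0.55 to 0.45 SD with a baseline covariate. That is worth the equivalent of 53 to 78 patients per arm instead of 40. About 18% of such trials would show a baseline imbalance of 0.3 SD or more, enough to move the unadjusted day-28 difference by 0.15 to 0.21 SD. These gains are upper bounds and shrink if pretreatment area is used as a covariate. As written, the plan also supports no per-patient change on the scale. Given the low cost of the remedy, the change should be made.

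**What to change.** - **Section 2.4:** state that the Pressure Ulcer Healing Scale is scored at enrolment, before allocation is revealed and before any wound cleaning or debridement, and again on day 28. If the full protocol already schedules an enrolment score, say so here.
- **Section 2.5:** compare day-28 scale scores between arms by ANCOVA with the enrolment score as covariate, and report each patient's change descriptively. State how curative effects and end-point efficiency are derived from the scale.
- **Table 1:** add pretreatment and post-treatment rows for the scale, so that sections 2.4 and 3 agree.

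The cost is one extra scale score, a few minutes per patient, and one form field, at the time the pretreatment sore area is recorded. No extra patients or procedures are needed.
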